## Abstract

**Background:**

The clinical decisions of emergency department triage nurses need to be of the highest accuracy. However, studies have found repeatedly that these nurses over- or underestimate the severity of patient health conditions. This has major consequences for patient safety and patient flow management. Workplace distractors such as noise and task interruptions have been pointed to as factors that might explain this inaccuracy. The use of a serious game reproducing the work environment during triage affords the opportunity to explore the impact of these distractors on nurse emergency triage accuracy, in a safe setting.

**Methods/design:**

A pilot study with a factorial design will be carried out to test the acceptability and feasibility of a serious game developed specifically to simulate the triage process in emergency departments and to explore the primary effects of distractors on nurse emergency triage accuracy. Eighty emergency nurses will be randomized into four groups: three groups exposed to different distractors (A, noise; B, task interruptions; C, noise and task interruptions) and one control group. All nurses will have to complete 20 clinical vignettes within 2 h. For each vignette, a gold standard assessment will be determined by experts. Pre-tests will be conducted with clinicians and certified emergency nurses to evaluate the appeal of the serious game.

**Discussion:**

Study results will inform the design of large-scale investigations and will help identify teaching, training, and research areas that require further development.

## Background

Patient safety is a key concern amid continuous efforts to improve the effectiveness and efficiency of health systems [1]. Defined as the “reduction of risk of unnecessary harm associated with health care to an acceptable minimum” [2] (p. 19), patient safety refers to the presence or absence of adverse events and/or medical errors and serves to compare the performance of health facilities worldwide [3]. Patient safety is strongly related to different nurse activities, particularly those where clinical decisions must be made [4, 5]. Clinical decision-making has been defined as “a contextual, continuous, and evolving process, where data are gathered, interpreted, and evaluated in order to select an evidence-based choice of action” [6] (p. 401).

Decision-making is a frequently performed process in emergency departments, especially in the course of triage, when nurses sort patients by care priority based on a process that aims for the best allocation of human and physical resources. It remains a human-driven process and as such is prone to error. Errors in clinical decisions can have serious consequences for patient safety [7, 8]. Underestimating the severity of a patient’s condition can lead to delayed emergency care and medical treatment that decreases the quality of the intervention [9]. Overestimating a patient’s condition results in inadequate resource allocation, which leads to overcrowding and work overloads in specific units [10]. With this in mind, nurses must arrive at highly reliable decisions and limit the occurrence of errors. What is more, nurses who perform triage must not only reach accurate decisions, they must also do so rapidly [11–13]. Indeed, decisions must be made within a very short time lapse (< 5 min) based on limited information and with limited access to peer clinical supervision [11, 14, 15].

To support nurses during the ED triage process and reduce errors, various scales have been developed since the early 1990s. Today, most of the existing triage scales cover four or five emergency levels [16–18]. Following these international standards, the Swiss Society of Emergency and Rescue Medicine currently recommended using the Swiss Emergency Triage Scale or SETS® [19] for ED patient triage. The SETS® has been psychometrically validated [10, 20] and is widely used in Switzerland, France, and Belgium. It spans four emergency levels from 1 to 4: acute, urgent, semi-urgent, and non-urgent. The introduction of triage scales has standardized nurse decisions and has facilitated the study of triage quality. Triage quality is most commonly assessed according to one indicator: accuracy. The accuracy of nurse triage decisions is measured by the degree of agreement between the emergency level assigned and a gold standard set by a panel of experts [21]. When nurses assign a level higher than the gold standard, it is referred to as overtriage [22, 23]. When the assigned level is lower, it is referred to as undertriage [9, 24].

In their systematic review, Farrohknia et al. [25] found the level of accuracy of nurse emergency level assignments to be medium to low. There has been little research, however, into the reasons for this relatively poor performance. The few studies that have investigated the issue have done so from the angle of nurse individual factors and contextual factors [26–28]. The individual factors considered include characteristics specific to nurses such as personality (flexibility, decision-making autonomy), cognitive processes (critical thinking, prompt decision-making), behavioral processes (working under pressure, being organized), and nurse experience (confidence in one’s decision-making) [28–30]. Where contextual factors are concerned, researchers have focused on the numerous distractors present in the environment [31–34], specifically frequent task interruptions, noise, and variable workloads. Any of these can result in the delayed performance of care activities, information loss, and a drop in concentration that alters the decision-making process, particularly when performing complex activities.

On a recurring basis, researchers who have examined the clinical decision-making of emergency nurses have generally used one of two approaches: retrospective reviews or nurse-assessed written clinical vignettes. Both methodologies have their shortcomings. For example, written vignettes present limited cues to make accurate decisions and retrospective reviews must cope with missing data [29, 35]. To reduce such biases, some authors [36] have underscored the importance of reproducing real-world conditions as faithfully as possible and of placing nurses in these circumstances. In this regard, the use of serious games (SG) simulating nursing tasks and the ED triage environment provides researchers with a unique opportunity to immerse nurses in such situations [35, 36] and investigate factors affecting triage, in a safe environment.

Nowadays, SG appear to be a solution for exploring clinical decision-making in the context of simulation [37, 38]. SG are defined as games whose primary purpose is neither fun nor entertainment. These are frequently used in the context of professional development and training, education, and scientific research [39, 40] to develop competencies in fields where poor decisions are associated with a high adverse-event risk, such as air traffic control [41] and the military [42]. More recently, SG have been used in the medical field to examine, for example, the impact of task interruptions on the medical evaluation of patients. Results have shown not only that these interruptions lengthen the duration of medical evaluations but also that subsequent decisions are more disorganized and deviate from prescribed standards [42].

The use of SG that reproduce an immersive ED environment and triage tasks allows assessing the impact of distractors on triage accuracy and represents an innovation in the field of triage quality improvement. Against this background, we are planning a pilot study to examine the preliminary effects of distractors on nurse emergency triage accuracy using an SG that we are developing specifically to simulate an ED environment. The study will have three main objectives: (1) develop the SG, (2) assess the feasibility and acceptability of our study design and the SG [43, 44], and (3) evaluate the primary effects of distractors on nurse emergency triage accuracy.

### Theoretical framework

The theoretical framework chosen for the study is an adapted version of the Systems Engineering Initiative for Patient Safety (SEIPS) model [45]. It is a framework frequently used in human factors analysis and patient safety research to gain insight on performance in different healthcare settings, including emergency departments [46–48]. The model comprises three dimensions: work system, processes, and outcomes. It has three main strengths. First, it can describe and operationalize the components of the work environment. Second, it can explain the interactions between the multiple components of the work system and the care processes. Third, it can demonstrate how the interactions between the work system and the care processes impact care outcomes. The model makes explicit the relationship between the work environment and the decision-making process. It distinguishes five components of the work system: person, tasks, tools and technology, environment, and organization.

Specifically, tools and technology refer to the elements that persons use to perform their tasks, such as a computerized care file, an electronic blood pressure monitor, and a telephone. ED studies have shown that technological breakdowns (computer downtime, blood pressure monitor out of order) can cause task interruptions [32, 49]. As this component is commonly explored when new technologies are introduced in the field of care, it will not be studied here, given that the nurses that will participate in the study are proficient in the use of the tools and technologies associated with the triage station.

The person component represents the core variable of the work system and refers not only to all the members of a team, which can include physicians, nurses, and other care providers, but also to the patients themselves and their families. In our study, the focus will be on nurses performing the task of emergency triage. For this component, Carayon et al. [45] recommended examining various elements, including personal, physical, and psychological characteristics, such as knowledge, motivation, and needs [45]. Triage studies have shown, in particular, that nurse education level, triage training, and work experience can influence triage accuracy, as can their aptitude to work fast and their confidence in their decision-making [28, 30, 35, 50].

The tasks component refers to the tasks to be performed by the person. In our study, the task corresponds to triage activities. Carayon et al. [45] proposed exploring elements of this component, such as the variety of tasks to be performed, job demands, and skills required to complete the task. ED studies [32] have identified one key element that disrupts the triage process: task interruptions. A task interruption is “an unexpected temporary or definitive halt to a human activity” [51] (p. 5, free translation). The presence of task interruptions diminishes the operator’s attention by causing it to be redirected elsewhere [32]. This can lead to a loss of information and to decision-making delays and errors [33, 52–54]. Within the framework of our study, the task interruptions that will be incorporated in the clinical vignettes, namely telephone calls, face-to-face communication, and patient requests, were chosen after consulting with the experts of the Swiss Triage Group.

The environment component refers to the physical environment. It is characterized by various elements, including noise, lighting, air quality, and workstation design. Among these elements, ED studies have identified noise as a factor that limits interaction between care provider and patient and as a potential distractor and stressor [31, 34, 55]. It can have a direct impact on productivity and safety in the workplace [56]. Noise is defined as an assortment of sounds perceived as annoying [57]. It is characterized by intensity (decibels), type (continuous, intermittent, variable), duration of exposure (time), and frequency [56]. Research has shown that nurses in emergency clinical units are exposed to continuous ambient noise of more than 65 dB, which exceeds the maximum noise levels recommended by the WHO for hospitals [58–60]. In our study, noise will be considered as a distractor and inserted directly in clinical vignettes. In order to examine the different noises present at an emergency triage station, we will, in conjunction with the experts of the Swiss Triage Group, document these noises through on-site recordings and then select the ones to which triage nurses are most commonly exposed.

The organization component refers to management style and time management, available resources, social relationships, and rules and procedures in place [45]. Nurse triage guidelines mention constraints that bear upon the task, especially limited time [61, 62]. Two studies [49, 63] carried out in European ED have demonstrated the mean duration of nurse triage to be 4 min. In our study, the time required by the nurses to determine the triage score for each clinical vignette will be measured and the variable will be considered in the analyses.

Though the SEIPS model focuses on the work system dimension, it also allows examining the dimensions of process and outcomes. The process dimension informs on the reasoning used by nurses to arrive at clinical decisions [64]. Within the framework of our study, there will be no in-depth examination of the decision-making process per se, only of the final outcome, that is, the SETS® scores (i.e., emergency level) that nurses assign to patients. Finally, the outcomes dimension will be analyzed in terms of accuracy of assigned emergency level. The pilot study will not examine the outcomes dimension in connection with employees and the organization.

### Purpose of the study

This pilot study has a double purpose. First, we wish to evaluate the acceptability and the feasibility of both our study design and the SG we developed to simulate the triage activity in an ED and reproduce an immersive work environment complete with distractors. Second, the study will also assess the preliminary effects of distractors (noise and task interruptions) on the triage accuracy of emergency nurses in the French-speaking part of Switzerland.

### Research questions

The questions asked in connection with the evaluation of preliminary effects are the following:
What is the acceptability level of our study design and the SG?What is the feasibility level of our study design and the SG?

The questions asked in connection with the evaluation of preliminary effects are the following:

Primary question:
What are the individual and combined effects of distractors on ED nurse triage accuracy?

Secondary questions:
2.How are nurse sociodemographic variables and personal characteristics related to triage accuracy?3.What is the relationship between nurse-perceived confidence and triage accuracy?

### Proposed hypotheses

We propose the following hypotheses informed by the SEIPS theoretical model [45]: (1) our protocol is easy to implement in a real-life situation and emergency nurses can easily participate and are happy to adhere to our study, (2) exposure to a distractor will lower nurse triage accuracy and inter-rater reliability, (3) exposure to two distractors will lower nurse triage accuracy and inter-rater reliability more so than exposure to only one distractor, (4) nurse work experience is positively related to triage accuracy, and (5) nurse-perceived confidence is positively related to triage accuracy.

## Method

### Study design

In order to evidence the effects of noise and task interruptions on nurse triage accuracy, we will carry out a 2 × 2 factorial randomized controlled trial [65]. A factorial design will be used given that two independent variables will be considered (noise and task interruptions) and that we will evaluate not only the effect of each variable on the dependent variable (nurse triage accuracy), but also their combined effect [65, 66]. The design will follow the CONSORT guidelines [67] and drive the structure of the trial and the choice of control, an analysis of study benefits, the quality and reliability of the intervention, a description of the population, the randomization procedure, and the statistical analysis plan.

This factorial design will allow us to create four groups: one control group and three experimental groups (A, B, C). While triaging the clinical vignettes, nurses in the control group will not be exposed to distractors. Nurses in experimental groups will be exposed to noise (group A), task interruptions (group B), or both noise and task interruptions (group C). Nurses will be block-randomized across the four groups by a computer program. The groups will be of equal size or as similar as possible in this regard.

The study design comprises repeated measures. We will collect sociodemographic and personal data from participants before they begin evaluating the clinical vignettes. Then, during the evaluation of each clinical vignette, the following data will be gathered systematically: (1) emergency level assigned, (2) level of perceived confidence in emergency level assignment, and (3) duration of each clinical vignette evaluation. Upon completing the evaluation of the 20 clinical vignettes, the participants will be asked to complete a questionnaire on the acceptability of the SG.

### Population and sampling

This multi-site study will be carried out in EDs where the SETS® is used. This is the case in 20 private and public care facilities in the five cantons of the French-speaking part of Switzerland (Geneva, Vaud, Fribourg, Jura, Neuchâtel). The population will consist of nurses who perform triage in these facilities. This corresponds to an accessible population of 454 nurses. The eligibility criteria will be similar to those used in previous studies of triage accuracy [27, 35, 68]. Specifically, to participate in our study, nurses must (1) consent to participate and (2) perform triage in one of the EDs where the SETS® is used. Nurses will be block-randomized across the four groups. We established a size of 20 nurses per group, for a total of 80. Around 18% of the accessible population is included, a non-negligible percentage that leaves, nonetheless, an ample margin for the recruitment for the future randomized control trial.

This sample size allows the inclusion of, at least, few nurses from each hospital providing an overview of all the emergency units of the hospitals in French-speaking Switzerland. Therefore, we can assume that our sample provides a sufficient heterogeneity to test acceptability and feasibility of our protocol. Moreover, assuming an accurate triage rate of 0.85 for the control group, a decline of 0.1 in the experimental groups, and an intraclass correlation (that is, between vignettes triaged by a same nurse) of no more than 0.03, we estimated through simulations that each group would need to comprise at least 20 participants to obtain a power of at least 0.80 in order to answer the primary research question. Consequently, we will aim to form a convenience sample of at least 80 nurses, and we will cease recruitment once this target is reached.

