### Data analysis plan

The nurse participants (expected *N* = 80) will be the analysis units for the descriptive analyses, and the assigned triage scale scores will be the analysis units for the correlational analyses and some descriptive analyses (number of nurses multiplied by number of vignettes—expected *N*: 80 × 20 = 1600). The following data analysis plan will be carried out to answer the research questions: First, the collected data will be verified (compliance with inclusion criteria, identification of missing data and outliers). Second, the data on the nurses (sociodemographic and professional) will be analyzed via descriptive statistics, both univariate (mean, median, standard deviation, interquartile range, and absolute and relative frequency) and bivariate (contingency table and marginal frequency). Third, triage accuracy will be measured by the level of agreement between the answers given by the nurses and the gold standard established by the experts. For each nurse, the scores assigned to each clinical vignette will be compared against the gold standard. The results of the comparison will be a three-level multinomial variable: accurate triage (nurse score same as gold standard), overtriage (score higher than gold standard), and undertriage (score lower than gold standard). Over- and undertriage frequencies will be used to describe the triage accuracy of the four groups, that is, the control group and the three experimental groups: noise (A), task interruptions (B), and noise and task interruptions (C). Fourth, to examine the individual and combined effects of the distractors on the triage accuracy of the nurse participants, the groups will be compared against one another using a random-intercept multinomial regression model. For all the analyses, the statistical significance level will be *p* ≤ 0.05. All the data will be analyzed using the R statistical software [79].

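### The stated power of at least 0.80 fits a group-versus-control or four-group overall test, but does not extend to the combined effect beyond a single distractor

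*Protocol article*

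**What the plan says.** All references are to the protocol article.

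- **Research questions.** The primary question is "What are the individual and combined effects of distractors on ED nurse triage accuracy". The Study design section gives the same two aims, each factor and their combination, as the reason for a 2 × 2 factorial trial.
- **Proposed hypotheses.** Hypothesis 3 is that "exposure to two distractors will lower nurse triage accuracy and inter-rater reliability more so than exposure to only one distractor".
- **Population and sampling.** The inputs are "assuming an accurate triage rate of 0.85 for the control group" together with "a decline of 0.1 in the experimental groups", and an intraclass correlation of at most 0.03 between vignettes of the same nurse. Simulations then showed that every arm "would need to comprise at least 20 participants to obtain a power of at least 0.80 in order to answer the primary research question". The simulated contrast is not named, and group C has no rate of its own.
- **Data analysis plan.** For the individual and combined effects, "the groups will be compared against one another using a random-intercept multinomial regression model". The level is fixed by "For all the analyses, the statistical significance level will be *p* ≤ 0.05", without saying whether tests are one- or two-sided.

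**The concern.** The power sentence covers the whole primary question, but its inputs describe one gap only: 0.85 in controls against 0.75 in every experimental group. They contain no difference between both distractors and one, and no interaction size is stated. The planning scenario and hypothesis 3 therefore disagree: with one common decline, adding the second distractor does no further harm.

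The results are meant to inform a larger study. Someone who relies on the power sentence could read a non-significant C-versus-A comparison, or a non-significant interaction, as a negative result obtained with 80% power. The design is not shown to have that power for either.

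**Working it through.** **Inputs.** From the article: 20 nurses per group, 20 vignettes per nurse, ICC 0.03 (the stated upper bound), control 0.85, A = B = C = 0.85 − 0.10 = 0.75, level 0.05. Assumed: two-sided tests and all 20 vignettes completed.

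**Effective size per group.** Design effect = 1 + (20 − 1) × 0.03 = 1.57. Effective n = 20 × 20 / 1.57 = 254.8.

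**The plan's own figure.** For one experimental group against control:

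- SE = √[(0.85 × 0.15 + 0.75 × 0.25) / 254.8] = √(0.315 / 254.8) = 0.0352
- Power = Φ(0.10 / 0.0352 − 1.96) = 0.81
- With 19 nurses, effective n is 380 / 1.57 = 242.0, the SE is 0.0361 and power is 0.79.

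So 20 per group is the smallest size that reaches 0.80, as the article states. A beta-binomial simulation with nurse-level t tests (20,000 runs) gave 0.80 for this comparison. In the same simulation, a four-group overall F test at 0.85/0.75/0.75/0.75 gave 0.81. The stated figure is therefore compatible with either test.

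**C against A (or B).** At the stated rates the difference is 0.75 − 0.75 = 0, so the rejection rate is simply 0.05. Any other rate for C is my assumption. Power = Φ(difference / SE − 1.96), with SE = √[(0.1875 + p_C(1 − p_C)) / 254.8]:

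| Rate in C | Difference from A | SE | Power |
|---|---|---|---|
| 0.75 (implied by the article) | 0 | 0.0384 | 0.05 (the test level) |
| 0.70 | 0.05 | 0.0395 | 0.24 |
| 0.65 (additive) | 0.10 | 0.0404 | 0.70 |
| 0.60 | 0.15 | 0.0410 | 0.96 |

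With a pooled variance under the null, the last three become 0.24, 0.69 and 0.95. In the simulation they were 0.24, 0.67 and 0.94. Showing C below both A and B is harder: at C = 0.65 the simulation gave 0.52.

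**Interaction at the stated rates.** On the risk-difference scale:

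- Size = C − A − B + control = 0.75 − 0.75 − 0.75 + 0.85 = 0.10
- SE = √[(0.1275 + 3 × 0.1875) / 254.8] = √(0.69 / 254.8) = 0.0520
- Power = Φ(0.10 / 0.0520 − 1.96) = 0.48

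On the logit scale, which is closer to the planned model, the power is 0.55. An interaction of the same size in the other direction (C = 0.55) has power 0.45 on the risk-difference scale and 0.14 on the logit scale.

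**The case against.** The strongest defence is that the number is right: it reproduces to the nurse, so there is no arithmetic error. Several stronger readings that a reader might infer are also not supported.

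- *That the 0.80 holds only for one group against control.* It does not. The overall four-group test also gives about 0.81, and the article does not say which contrast was simulated. Under additive effects (C = 0.65), a factorial main effect, 40 nurses against 40 at 0.80 against 0.70, would have power 0.96. At the article's own rates that contrast has only 0.48.
- *That combined exposure has no assumed effect.* It has one. The decline of 0.1 applies to all experimental groups, so C against control has power 0.81. If "combined effect" means only that comparison, the claim is met. What is missing is an effect of C beyond A or B.
- *That C against A is necessarily weakly powered.* That depends on a rate the article does not give. A rejection rate of 0.05 at C = 0.75 reflects a true null, not a weak design.
- *That the model must be rewritten with factorial terms.* With four cells, a four-group model and a model with noise, interruption and their product are the same model in two parameterisations. Comparing groups with one another already allows C − A and C − B.

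It is also fair to say that this is a pilot, that effects are called preliminary, and that the sample is first justified on feasibility grounds.

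All of this narrows the point but does not remove it. The article chose to claim formal power for the full primary question and to test at 0.05. The factorial rationale and hypothesis 3 both go beyond C against control, and hypothesis 3 conflicts with the planning rates whatever the simulated test was.

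**Conclusion.** The point holds in this limited form. The power of at least 0.80 is correct for an experimental group against control, or for an overall four-group test. It does not cover the effect of two distractors beyond one. At the plan's rates the interaction has power of about 0.48 (0.55 on the logit scale), and hypothesis 3 is false by assumption. If C is lower than A and B, power for C against A is about 0.24, 0.70 or 0.95 at C = 0.70, 0.65 or 0.60, so even additive effects leave it below 0.80.

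These figures rest on two-sided testing, ICC at its stated bound of 0.03, all vignettes completed, normal approximations, and rates for C that I assumed. The documents do not support calling the sample size miscalculated or the model wrong. The fault lies in the scope of the power sentence and in its conflict with hypothesis 3.

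**What to change.** In Population and sampling:

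1. Name the contrast behind the 0.80: each experimental group against control, or the overall four-group test if that was what was simulated. State that tests are two-sided, if they are.
2. Give group C an assumed rate consistent with hypothesis 3, with a reason, and report the resulting power for C against A and C against B from the same simulation program.
3. State that the interaction is not powered at 0.80 and will be reported as an estimate with a confidence interval.

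No extra nurses and no change of model are needed. The cost is a rerun of the simulations for the added contrasts and a less favourable power statement.
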